### Recruitment

For the *in silico* development stage, all cases will be recruited at the Eye & ENT Hospital of Fudan University. Specifically, researchers will record doctor-patient conversations at each subspecialty clinic. The conversations will undergo a curation process that involves the removal of filler words and irrelevant content, resulting in the creation of medical dialogues. Eligible medical dialogues will be continuously enrolled from June 1 to July 1, 2023. Regarding the anterior segment images, researchers will browse medical records and consistently gather images related to the top 1–5 diseases in each subspecialty from January 1, 2020 to July 1, 2023. The initial sample size consists of 20 dialogues per specialty and 50 images per disease, which is then adjusted according to the AI system's performance.

For the silent evaluation stage, data will be continuously gathered in Shanghai from July 10 to July 15, 2023, with a sample size of 100 cases. Two pre-trained researchers will serve as observers in outpatient clinics, ensuring they do not interfere with standard management procedures. Upon obtaining the patients' consent (as detailed in Supplementary material 2), the researchers will collect the patients' medical information and enter it into the system. For patients who are prescribed with anterior segment imaging test by outpatient clinic doctors, the researchers will collect the images from the electronic medical system.

For the early clinical evaluation stage, eligible participants will be continuously recruited at three distinct sites. The Shanghai site serves as an internal validation dataset, with data collection spanning from July 21 to August 20, 2023. The Nanjing and Suqian sites function as external validation dataset, with data collection scheduled from August 21 to August 31, 2023. Each center will be staffed with two pre-trained researchers. These researchers will be responsible for patient recruitment across various subspecialty clinics within their respective centers. Once patients provide their consent (as detailed in Supplementary material 4) to participate in the study, the researchers will gather medical history and acquire anterior segment images. Following this, outpatient physicians will proceed with clinical diagnosis and treatment.

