#### Early clinical evaluation

The mobile mini-program will be upgraded to analyze anterior segment images obtained by smartphone-based devices. An early clinical evaluation of this upgraded program will be simultaneously conducted as a cross-sectional study at three sites: the Eye & ENT Hospital of Fudan University (Shanghai), the Affiliated Eye Hospital of Nanjing Medical University (Nanjing), and Suqian First People's Hospital (Suqian). During the study, researchers will interact with patients to collect necessary information for completing the queries generated by the AI system. Anterior segment images will be captured for each patient by researchers using smartphones (Figure 4). The images should be captured by the macro lens of the smartphone. The positions of both eyes should align with the eye locations specified on the smartphone screen. The images should be large enough to provide a clear view of the affected area of the diseased eye. For all stages, the reference standards of disease diagnoses and subspecialty triage will be determined by an expert panel comprising ophthalmic specialists with a minimum of 5 years of clinical experience. Upon the completion of these data collections, a separate expert panel will assess the accuracy of AI intelligent diagnosis and triage.

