### Eligibility criteria

Medical dialogues in the development stage should comply with the following criteria: (1) Inclusion criteria: We will include dialogues from both initial consultations and follow-up visits that provide adequate medical history information while minimizing the inclusion of physical examination details. The diagnosis should correspond to diseases ranked within the top 5 outpatient cases for each subspecialty, based on data from the Eye & ENT Hospital of Fudan University over the past 3 years. (2) Exclusion criteria: we will exclude diseases that are diagnosed or triaged solely based on physical examinations.

Anterior segment images in the development stage should comply with the following criteria: (1) Inclusion criteria: Individuals should have a documented medical history and diagnosis; Following a review of the medical history, both the diagnosis and subspecialty triage should have been confirmed according to the reference standard, as specified below. (2) Exclusion criteria for anterior segment images: photos with insufficient lighting or facial covering.

In the silent evaluation and early clinical evaluation stages, all cases should adhere to the following criteria: (1) Inclusion criteria: informed consent must be obtained from all participants; participants should have specific concerns or issues directly related to their eyes; for patients who are unable to provide informed consent due to incapacity or are underage or otherwise vulnerable, consent from must be obtained from their legal guardians and legal guardians are required to assist in the collection of medical history and images; each participant's diagnosis and subspecialty triage must be validated using a reference standard as detailed below. (2) Exclusion criteria: cases where the diagnosis and triage results fail to generate due to a program error; patients who, in the opinion of the attending physician or clinical study staff, are too medically unstable to participate in the study safely; diseases with prevalence below the 5-percentile threshold are not included.

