### Reference standard

The reference standard is determined by an expert panel comprising five senior consultants (with a minimum of 5 years of clinical experience). A consensus of diagnosis and triage is required from at least three out of these five experts after a comprehensive review of the patients' medical histories. In cases where expert consensus cannot be achieved, patients will be asked to attend follow-up appointments, during which additional examinations may be recommended. If, after 3 months of follow-up, a definitive diagnosis remains elusive, the patient will be excluded from the study.

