### Sample size calculation

In the *in silico* development stage, the sample size is adjusted based on AI system performance. Initially, each subspecialty involves 20 medical dialogues, with 80% for training ChatGPT and 20% for validation. If ChatGPT cannot generate inquiries, diagnoses, and triage results in the validation dataset, we'll increase the dialogues. Next, 50 virtual cases for the top 1–5 diseases in each subspecialty are input into the diagnostic system. If the sensitivity and specificity of specific diseases do not meet the predefined thresholds (sensitivity ≥ 90%, specificity ≥ 95%), we will proceed to develop a disease-specific image-based diagnostic system. For each disease, we will compile a dataset consisting of 50 cases, including both anterior segment images and their corresponding diagnoses. This dataset will be randomly partitioned into training and testing sets, with the training set supporting system development and the testing set assessing diagnostic accuracy. Should the predetermined criteria (sensitivity ≥ 90%, specificity ≥ 95%) be satisfied, there will be no necessity for further expansion of the sample size.

For the silent evaluation stage, the primary objective is to achieve a sensitivity ≥ 85% and specificity ≥ 95% for diagnosing ophthalmic diseases. To meet this goal, we set sensitivity = 0.85, specificity = 0.95, statistical power (1-β) = 85, significance level (α) = 0.05, and the sample size for each disease is determined to be 22, following the methodology (Tests for One-Sample Sensitivity and Specificity) outlined in Pass15. Since this stage covers at least four different illnesses, we will include a minimum of 88 patients in the entire sample. To account for potential confounding factors, we have opted to include 100 patients in this phase.

For the early clinical evaluation stage, all subjects collected within predefined date ranges at three sites will be included. Data collection at the Shanghai and Nanjing sites spans from July 21 to August 20, 2023. At the Suqian site, data collection is scheduled from August 21 to August 31, 2023.

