### Data management

The research consortium organizes a central data management board, and the contact details of its members can be obtained from the consortium coordinator, [name]. Electronic medical records data for all recruited subjects will be securely stored in password-protected files on the hospital's local server. Access to these files will be restricted to researchers with the explicit consent of the subjects. Survey data, both input and output from the multimodal AI system, will be stored in a secure public server (aliyun.com). To safeguard patient privacy, we will not collect any Protected Health Information (PHI), including the patient's name, date of birth, and medical insurance number. The anterior segment images captured by either slit-lamp or smartphones will undergo digital masking to irreversibly remove identifiable features, while preserving disease-relevant features essential for diagnosis. To further ensure data security, clinical researchers, trained in data management, will utilize password-protected smartphones for data entry. The smartphone is securely stored in a cabinet with password protection and is not permitted to be taken outside of the research site. Data integrity will be rigorously maintained through a variety of mechanisms, including referential data rules, valid values, range checks, and consistency checks against data already stored in the database.

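### The evaluation-stage criteria neither exclude Shanghai patients who helped build the system nor limit each person to one entry

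*Protocol article*

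**What the plan says.** The Recruitment section states that for development "all cases will be recruited at the Eye & ENT Hospital of Fudan University". It sets the dialogue window ("Eligible medical dialogues will be continuously enrolled from June 1 to July 1, 2023") and takes images from that hospital's medical records from January 1, 2020 to July 1, 2023. The silent evaluation follows in Shanghai on July 10 to 15, with 100 cases. For the next stage, "The Shanghai site serves as an internal validation dataset, with data collection spanning from July 21 to August 20, 2023". The Early clinical evaluation section names the Eye & ENT Hospital as the Shanghai site.

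Under Eligibility criteria, the development rules accept returning patients: "We will include dialogues from both initial consultations and follow-up visits". For the two evaluation stages, inclusion needs consent, an eye-related concern and a reference-standard diagnosis and triage. The exclusions are program error, medical instability and low-prevalence disease. Earlier participation and repeat entry are not mentioned. The Sample size calculation section says that for the early clinical stage "all subjects collected within predefined date ranges at three sites will be included".

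The Reference standard section says that when the panel cannot agree, "patients will be asked to attend follow-up appointments, during which additional examinations may be recommended", with a limit of 3 months. The Outcome measure section allows early clinical patients, after they have rated satisfaction, to learn the reference result and whether the system was right.

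**The concern.** A validation set should consist of people the system has not seen. Here the pool that supplies development material also supplies both Shanghai evaluations, and only dates separate them. A chronic eye patient photographed in 2022 or recorded in June 2023 can attend again in July or August with the same eye and the same disease.

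Two things are at stake. First, if contributors are easier for the system than new patients, Shanghai sensitivity is biased upward. Nanjing and Suqian are not exposed to this route, so part of any gap between internal and external validation could reflect overlap and not a failure to generalise. The silent evaluation has no unexposed site to compare with. Second, a person who re-enters within the Shanghai month gives two correlated records in one dataset. On the second occasion that person may already know the panel's diagnosis and can repeat it when answering the system's questions.

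**Working it through.** No figure in the article is in dispute. The check compares the windows, the criteria and the material used at each stage.

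**Windows (Recruitment)**

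| Stage | Source | Window (2023 unless stated) | Image type |
|---|---|---|---|
| Development dialogues | Eye & ENT Hospital | June 1 to July 1 | none |
| Development images | same hospital, medical records | January 1, 2020 to July 1, 2023 | slit-lamp or camera in the facility |
| Silent evaluation | Shanghai | July 10 to 15 | facility image from the electronic record |
| Early clinical, Shanghai | Eye & ENT Hospital | July 21 to August 20 | new smartphone image |

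The silent stage is stated only as Shanghai, but this hospital is the only Shanghai site named.

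**Possible returns**
- June dialogue patient into the silent stage: July 1 to July 10 = 9 days at least; June 1 to July 15 = 44 days at most.
- June dialogue patient into the Shanghai early clinical stage: July 1 to July 21 = 20 days; June 1 to August 20 = 80 days.
- Silent-stage patient into the Shanghai early clinical stage: July 15 to July 21 = 6 days; July 10 to August 20 = 41 days. The 3-month recall period for unresolved silent-stage cases covers this whole window.

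These are ordinary follow-up intervals, and no listed criterion stops the person at entry.

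**Strength of each route**
1. Development image to silent evaluation: same equipment type, same record system, same eye. This is the strongest route.
2. Development image to early clinical evaluation: a new smartphone photograph read by an upgraded program. Weaker.
3. Development dialogue to either evaluation: dialogues shape prompts and question lists, and the later consultation is a new one. Probably weak.
4. Silent to early clinical evaluation: the article does not say that silent-stage cases tune the diagnostic function. This route leads to leakage only if they do.
5. Re-entry within the Shanghai month: needs no training effect, because the patient may know the reference result.

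**Size (illustration only).** Let f be the share of test patients who contributed earlier, s₀ the sensitivity in new patients and s₁ that in contributors. Observed sensitivity = (1 − f)s₀ + f·s₁, so the bias is f(s₁ − s₀). None of the three inputs is in the article.

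| Assumed s₀, s₁ | Stage goal | f = 5% | f = 10% | f = 20% | Overlap at which the goal is reached |
|---|---|---|---|---|---|
| 0.80, 0.95 | 85% (silent) | 0.8075 | 0.815 | 0.830 | 0.05/0.15 = 33% |
| 0.72, 0.95 | 75% (early clinical) | 0.7315 | 0.743 | 0.766 | 0.03/0.23 = 13% |
| 0.70, 0.95 | 75% (early clinical) | 0.7125 | 0.725 | 0.750 | 0.05/0.25 = 20% |

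At 5% to 10% overlap the bias runs from 0.05 × 0.15 = 0.75 points to 0.10 × 0.25 = 2.5 points. The early clinical rows treat 75% as a Shanghai goal. The Hypotheses section sets it for the stage, so pooling with the two unexposed sites would dilute the effect.

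**The case against.** The article is condensed, and a duplicate check at enrolment could sit in a fuller protocol. That would carry weight if eligibility were only summarised. Here the evaluation criteria are itemised, so the gap is in text that is present.

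The training mechanism is also weaker than it first appears. Dialogues serve prompt engineering, image models are built only for diseases that miss the text-only thresholds, only the training part of each image set builds them, and the early clinical stage uses a different device. This stands and limits the likely size. It does not cover the silent stage, where the image type and record system are the same as in development.

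A reader might infer several stronger things that the documents do not support:
- That overlap can never be traced. Names, birth dates and insurance numbers are kept out of the study data, but medical records of recruited subjects are held on the hospital server and individual patients can be recalled for follow-up. Hospital-side linkage therefore exists.
- That people are counted twice across stages. The silent and early clinical stages have separate targets and are nowhere pooled, so double counting can arise only within a stage.
- That stated confidence intervals are invalidated. The Statistical analysis section names no intervals.
- That the fine-tuning under Adverse event monitoring feeds evaluation cases back into diagnosis. It concerns toxic content.
- That recalled patients are re-enrolled. They return to settle an existing case; re-enrolment is possible, not planned.

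The labels internal and external validation, and the Limitation section's warning that case mix differs by centre, also make a naive reading of a Shanghai gap less likely. They do not separate case mix from overlap.

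**Conclusion.** The point holds in a limited form. Followed exactly, the plan allows a development contributor to be a Shanghai test case and allows one person to enter the Shanghai set more than once. The exposure is greatest in the silent evaluation and smaller in the smartphone stage. Only Shanghai is affected, and any bias would favour it over Nanjing and Suqian.

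The size cannot be computed from the article and is probably modest. The 13%, 20% and 33% crossing points rest wholly on assumed sensitivities. They do not show that any goal would be reached falsely, since nothing in the article suggests how large the overlap is. The change is worth making because it is cheap and protects the independence that the word validation implies, not because a large bias has been shown.

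**What to change.** Add to the evaluation-stage exclusions under Eligibility criteria: *patients whose image or dialogue was used in development, or who were already enrolled in the silent or early clinical evaluation; each patient is entered once, at the first eligible visit.*

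At Shanghai, check the hospital record number at enrolment against hospital-held lists of development and earlier evaluation patients. The check stays inside the hospital system, so no identifier enters the study data. If enrolment has already taken place, run the same check retrospectively on the hospital side, remove overlapping cases from the analysis and report how many there were.

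The cost is one criterion, a lookup at one site and the loss of a few returning Shanghai patients.

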### Blinding

The blinding methods vary depending on the roles of the researchers and the stage of the study in which the researchers and subjects are involved. AI developers and AI output correctness assessors have access to complete patient information, including medical history, reference standard results, and AI output for determining correctness.

In our study, two roles are subject to blinding. (1) Reference standard assessors: These assessors possess knowledge of the patient's clinical information but are unaware of the AI output or its correctness. This approach helps mitigate information bias and classification bias. (2) Clinical researchers: These researchers are responsible for inputting data into the multimodal AI program. During the *in silico* development stage, they have access to all patient clinical information and reference standard results. However, during the silent evaluation and early clinical evaluation stages, they only have access to the patient's clinical information without knowledge of the reference standard. This approach helps mitigate diagnostic suspicion bias.

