### Implementation

Clinical researchers responsible for AI system input data play a crucial role in influencing the research outcomes. Our implementation strategies focus on training researchers to minimize human-induced confounding bias. In the *in silico* development stage, researchers are required to hold a PhD in Ophthalmology from Fudan University and have at least 3 years of clinical experience as attending physicians. Prior to implementing the study, they must have completed rotational training in various ophthalmic subspecialties to ensure proficiency in medical inquiry, diagnostic criteria, and medical record documentation for common ophthalmic diseases.

During the silent evaluation and early clinical evaluation stages, clinical researchers will be junior university students specializing in clinical medicine at Fudan University. They will receive training in ophthalmology-related terminology and patient communication, enabling them to explain medical terms to patients and provide accurate responses to the AI system's queries. Data collection across the three research sites will be conducted by the same group of researchers.

For anterior segment image captured in medical facility, the technicians should possess a minimum of two years of experience to ensure precise lesion capture with appropriate lighting conditions. The researchers responsible for smartphone-based images should be pretrained to capture clear anterior segment images with smartphones.

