## Discussion

Our study aims to develop a multimodal AI system based on ChatGPT-3.5 and explore its performance for the diagnosis and triage of ophthalmic diseases. Existing alternative proprietary LLMs include ChatGPT-4.0 and Google Bard (Lim et al., 2023). Additionally, there are some open source LLMs that can be locally deployed. As we plan to apply our designed multimodal AI system in clinical experiments, it necessitates swift interactive responses and the ability to handle parallel tasks. There are two primary reasons for not utilizing locally deployed LLM models. Firstly, their text generation performance is not as robust as ChatGPT, which hinders rapid interaction and concurrent conversations. Secondly, it demands a substantial amount of data for initial local training, which doesn't align with our objective of rapid product development and application in clinical experiments. ChatGPT currently stands out as the most proficient and reliable LLM product on the market for interactive applications. While ChatGPT-4.0 lacks support for prompt engineering, and Google Bard was not yet available at the outset of our research, we made the decision to develop our multimodal AI system based on ChatGPT-3.5.

One of the strengths of our multimodal AI system is its applicability to different ophthalmic diseases. Previous studies predominantly rely on photographs to detect certain ocular and visual abnormalities (Ting et al., 2019; Tan et al., 2021; Tiwari et al., 2022; Lou et al., 2023; Shao et al., 2023a). These image-centric technologies, while valuable, have limitations when it comes to large-scale applications across diverse ophthalmic conditions. The limitations primarily stem from the absence of comprehensive medical histories, which are crucial for accurate diagnosis (Ting et al., 2019; Moor et al., 2023). Therefore, we aim to integrate medical history inquiry with image-based diagnosis to empower a multimodal AI system. According to the protocol, we will evaluate the performance of this system in detecting most of the common ophthalmic diseases, including anterior and posterior segment disorders, strabismus, neoplasms, aesthetic abnormalities and ocular manifestations of systemic diseases. This system is efficient for triage procedures. During registration, pre-registration desk staff can assist patients with AI-powered diagnosis and triage, guiding them to subspecialty appointments.

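### In the early clinical stage, operators recruit inside subspecialty clinics, so they see a strong proxy for the triage answer, and triage is tested only in patients already routed to a clinic

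*Protocol article*

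**What the plan says.** All references are to the protocol article.

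- **Where patients are found (Recruitment).** Each center has two trained researchers for the early clinical stage. "These researchers will be responsible for patient recruitment across various subspecialty clinics within their respective centers".
- **Who produces the AI's input (Recruitment, Early clinical evaluation, Implementation).** After consent, "the researchers will gather medical history and acquire anterior segment images". In doing so, "researchers will interact with patients to collect necessary information for completing the queries generated by the AI system". Their training is described as "enabling them to explain medical terms to patients and provide accurate responses to the AI system's queries".
- **Timing (Recruitment).** The AI session comes before the clinic physician sees the patient: "Following this, outpatient physicians will proceed with clinical diagnosis and treatment".
- **Blinding.** In both evaluation stages, operators are masked in the sense that "they only have access to the patient's clinical information without knowledge of the reference standard". The stated purpose is: "This approach helps mitigate diagnostic suspicion bias". The clinic attended is not mentioned.
- **Outcome and target (Outcome measure, Hypotheses, In silico development).** Correct triage is the secondary outcome. The early clinical targets are PPV ≥80% and NPV ≥95%. Ten subspecialties are listed.
- **Reference standard.** Triage is set by agreement of at least three of five experts, not by the clinic attended.
- **Proposed use (Discussion).** "During registration, pre-registration desk staff can assist patients with AI-powered diagnosis and triage, guiding them to subspecialty appointments".

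**The concern.** The operator is not a passive recorder. The operator talks to the patient, explains terms and supplies the answers to the system's questions. An operator recruiting in a glaucoma or strabismus clinic knows which category the patient has been sorted into, and that category is one of the possible triage answers. The knowledge can affect which complaint is entered first, which details are stressed and how an unclear answer is phrased. The blinding is meant to prevent this kind of influence, but it is defined only against the panel's result.

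Sampling raises a second issue. Patients reach the study after someone has chosen a clinic for them, or they have chosen one themselves. The Discussion proposes the tool for use before that choice. Patients who do not know where to go may be less common in the sample than at a registration desk.

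What is at stake is how the triage result can be read. Meeting the targets would not by itself show that the system adds triage information beyond the clinic attended, or that it would perform as well at registration.

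**Working it through.** The plan gives no figure for this point, so there is none to reproduce. The check compares sections and then uses three short illustrations whose inputs are assumptions.

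**1. Sections side by side.** Recruitment puts the operator in the subspecialty clinic. Early clinical evaluation and Implementation let the operator shape the answers. Blinding hides the panel's result and nothing else. Holding the AI session before the physician's diagnosis keeps that diagnosis out of the input, but routing has already happened. The Eligibility criteria ask for an eye complaint and do not require a new or un-triaged patient. The Limitation section mentions case-mix differences between centers and restricted transfer to community or home settings. It names neither prior routing nor the operator's knowledge of the clinic.

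**2. What a clinic-attended rule would score.** Let *a* be the share of patients whose clinic matches the panel's triage. Assume one label per patient and pool the one-vs.-rest tables over 10 categories. A correct label contributes 1 true positive and 9 true negatives. A wrong one contributes 1 false positive, 1 false negative and 8 true negatives. Then:

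- pooled PPV = a / (a + (1 − a)) = a
- pooled NPV = (9a + 8(1 − a)) / (9a + 8(1 − a) + (1 − a)) = (8 + a)/9

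| a (assumed) | pooled PPV | pooled NPV |
|---|---|---|
| 0.80 | 80% | 8.80/9 = 97.8% |
| 0.85 | 85% | 8.85/9 = 98.3% |
| 0.95 | 95% | 8.95/9 = 99.4% |

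PPV ≥80% needs a ≥ 0.80. NPV ≥95% needs 8 + a ≥ 8.55, so a ≥ 0.55. PPV is the binding target. Values for single subspecialties would differ. This is a yardstick for reading the targets; it does not estimate bias in the AI's results.

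**3. What leakage could do.** Let *q* be true triage correctness and *L* the share of otherwise wrong results put right by knowledge of the clinic. Observed correctness = q + (1 − q)L. With q = 0.70 (assumed), L = 0.10, 0.25 and 0.50 give 0.73, 0.775 and 0.85. With q = 0.60, they give 0.64, 0.70 and 0.80. The documents give neither q nor L, so this shows direction only.

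**4. Why the figures do not carry over to registration.** PPV = Se·p / (Se·p + (1 − Sp)(1 − p)), where p is a subspecialty's share of participants. Taking Se 0.75 and Sp 0.95 (the stage's diagnosis targets, borrowed here for triage as an assumption):

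| p | PPV | NPV |
|---|---|---|
| 2% | 0.23 | 0.995 |
| 10% | 0.63 | 0.972 |
| 20% | 0.79 | 0.938 |
| 40% | 0.91 | 0.851 |

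PPV reaches 0.80 at p of about 21%. The result depends on a case mix that follows from which clinics the researchers visit.

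**The case against.** The strongest reply is that the plan's blinding statement is literally true. The triage reference is a panel consensus and operators do not see it. Knowing a proxy is not knowing the standard. This stands: the Blinding section is incomplete, not false, and a reader who infers that it is contradicted goes too far.

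Second, the clinic is not described as an input to the system. The inputs are the complaint, the answers to generated questions and the images. The AI cannot simply repeat the clinic, so the benchmark's score does not measure inflation. This also stands. Leakage could act only through how complaints and answers are put, by students trained in terminology and communication. A reader might infer that triage performance will be overstated; the documents support only that it may be.

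Third, a patient waiting in the wrong clinic has not yet been redirected at that visit and can still be enrolled. General ophthalmology and ophthalmic emergencies, two of the ten categories, may be little pre-sorted. The documents do not say how patients reach a clinic. Some depletion of misrouted patients is plausible, but its extent is unknown.

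Fourth, this stage's objective is performance in outpatient clinics, and the registration desk appears only in the Discussion. That narrows the point without removing it, because the use is put forward and the limitations do not say it is untested.

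Finally, it is tempting to conclude that recruitment must move to registration. That does not follow. Sampling across clinics is a defensible way to cover ten subspecialties in short windows (11 days at Suqian, August 21 to 31), and registration enrolment could leave low-volume subspecialties sparse.

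**Conclusion.** The point holds in a limited form. Operators who shape the AI's input can see a strong proxy for the triage outcome, the stated blinding does not address it, and participants have already been routed. Triage PPV and NPV may therefore be overstated, and the results will not directly support use before a clinic is chosen.

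The size of any inflation cannot be derived. What can be said is that repeating the clinic attended would meet both pooled targets if at least 80% of patients are in the clinic the panel names, assuming one label per patient and ten categories. That the clinic is a strong proxy is a reasonable inference, not a documented fact. The issue falls mainly on the secondary triage outcome; clinic context might also inform the primary diagnosis outcome, but less directly. A modest addition to data capture and reporting is enough.

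**What to change.** Keep the recruitment plan and make four additions:

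1. Record the recruiting clinic for every participant in the early clinical stage.
2. Report triage separately for participants whose clinic does and does not match the panel's triage. The mismatch group is the informative one, because there the clinic cue points away from the reference. Lower accuracy in that group would not prove leakage, since these patients may also be harder to triage.
3. For the whole sample, show a benchmark in which triage is set to the clinic attended, using the same one-vs.-rest PPV and NPV as for the AI.
4. State under Blinding that operators are not masked to the clinic, and limit the triage conclusion to already-routed outpatients.

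The cost is one data field, one extra table and a narrower triage claim. The mismatch group will probably be small and its estimates imprecise. This stage takes everyone within its date windows and sets no target number, so the size of that group cannot be fixed in advance.

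Enrolling at registration, before the clinic is chosen, would test the proposed use directly. It is an option to weigh against subspecialty coverage, not a required change.
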